**REVISION HISTORY**

| **Revision #** | **Version Date** | **Summary of Changes** | **Consent Change?** |
| --- | --- | --- | --- |
| 2.1 | 04Aug2020 | Transferred from old IRB format to new format using Form 503 | No |
| 2.2 | 04Aug2020 | Updated to include option for subjects to submit video evidence of motor skill attainment for remote visits | Yes |
|  |  |  |  |
|  |  |  |  |
|  |  |  |  |

# Study Summary

| **Study Title** | Exploring the feasibility and utility of in-home body weight support harness system use in children treated for spinal muscular atrophy |
| --- | --- |
| **Study Design** | Pilot interventional study |
| **Primary Objective** | Investigate whether BWSS is a feasible option for in-home exercise and investigate the use of home-based functional exercise using a body weight support harness system (BWSS) on motor performance in children treated for spinal muscular atrophy |
| **Secondary Objective(s)** | Explore influence of frequency of use on change in motor performance over 6 months. |
| **Research Intervention(s)/ Investigational Agent(s)** | Enliten, LLC portable body weight support harness system (BWSS) |
| **IND/IDE #** |  |
| **Study Population** | Children who have been treated for spinal muscular atrophy |
| **Sample Size** | Up to 50 children |
| **Study Duration for individual participants** | On-going; each child will be followed for six months with possibility of extension. |
| **Study Specific Abbreviations/ Definitions** | BWSS – body weight support harness system  SMA – spinal muscular atrophy |

# Objectives

- 1. The purpose of the study is to investigate the feasibility and utility of using an in-home body weight support harness system (BWSS) to promote motor performance in children who have been treated for spinal muscular atrophy. Our primary aim is to explore whether BWSS is a feasible modality for in-home use and whether it impacts motor performance. Our secondary aims are to determine whether frequency of BWSS impacts treatment effect.

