# Background

- 1. Spinal muscular atrophy (SMA) is an autosomal recessive disease involving the degeneration of lower motor neurons in the spinal cord that results in progressive muscle atrophy.1 SMA is characterized into four main phenotypes based on age of onset and highest motor milestone achieved: type I (unable to sit unassisted); type II (able to sit unassisted but unable to stand or walk independently); type III (walks independently); and type IV (adult-onset).2 Historically, a multidisciplinary treatment approach is aimed at limiting the trajectory of decline through proactive management of clinical manifestations.3,4 With newer technologies providing improved supportive care, it has been hypothesized that the expected phenotype for all types of SMA is evolving toward improved survival and optimized function.5 This maintenance approach to symptomatic management is also being driven to change as recent therapeutic advancements are making their way through the clinical trial pipeline. In December 2016, Spinraza® (nusinersin) became the first US FDA approved drug available for the treatment of SMA.6 This was quickly followed by the promising preliminary results for AVXS-101 gene replacement therapy in children with SMA type I, which reported subject achievement of gross motor milestones beyond what would be expected for their diagnosis.7 Both therapies target the preservation of existing motor neuron connections in the spinal cord and provide greater evidence for a changing phenotype of symptom stabilization and functional improvement that will require a new approach to clinical care.
  2. Physical therapists play a key role in the evaluation and management of musculoskeletal manifestations and functional impairments in children and adults with SMA. Recently published care guidelines stratify suggested categories of physical therapy assessment and interventions by functional ability (non-sitters, sitters, and ambulatory).3 These guidelines were created prior to this new treatment-era of SMA and are aimed at supporting the highest level of function, not towards facilitating development of strength, skill, and more advanced motor milestones. The reported success of SMA drug therapies suggest physical therapy interventions may now be aimed at motor milestone and gross motor development.

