# Procedures Involved*

- 1. This is a voluntary study investigating the feasibility and effects of a home-based functional exercise program using a body weight support harness system (BWSS) on motor performance in children treated for spinal muscular atrophy. Subjects will be provided with one portable BWSS, manufactured by Enliten LLC, to be used in their home for a period of 6 months. Subjects will engage in a BWSS use and document frequency / duration of use.
  2. **Screening/Baseline**: Subject demographic information and equipment safety check will be completed prior to the initial in-home visit. Baseline assessment of motor function may be completed at any time within a 3 week window prior to or during the initial in-home visit.

**Initial Visit (in-home):** A study team member will travel to the subject’s home to complete the BWSS set up. The BWSS Inspection Check List will be reviewed and signed by the responsible participating family member and the study team member. Pictures or video of the final set-up will be taken and stored in the subjects file. The participating family members will be trained on how to securely strap their child into the harness and on appropriate activities to engage in with their child while in the harness. They will be instructed on frequency and duration of treatment time and asked to document this information in the Daily Activity Log. They may be asked to attach an activity monitor to the harness.

Prior to completion of this visit, the following documentation will be completed: 1) Informed Consent; 2) BWSS Inspection Check List; 3) Pictures or video of BWSS set-up in home.

A study team member will contact the family between the baseline and midpoint assessment visit to ensure the family is comfortable with BWSS use. If the family has questions or concerns, they will be addressed by the study team member via Skype or video conference phone call. If determined necessary by the PI, a study team member will travel to the family’s home for an additional in-home visit.

**Midpoint Assessment Visit**: A study team member will complete functional outcome assessments and evaluate compliance with usage schedule. Daily Activity Log will be checked and completion will be documented.

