# Inclusion and Exclusion Criteria*

- 1. Subjects will be screened during regular clinic visits, by review of inclusion/exclusion criteria in correspondence with family, and/or prior to enrollment and informed consent process.
  2. **Inclusion criteria:** Able to safely fit in pediatric harness; genetic diagnosis of spinal muscular atrophy, delay in standing or walking, able to right head from full flexion, treatment with a disease modifying agent

**Exclusion criteria:** At any point during interventional period of the study, a body weight greater than 50 pounds (lbs) or 22.68 kilograms (kg); evidence of current or previous unresolved lower limb injury, current or recurrent fractures within the past 6 monhts that could affect performance or study procedures; medical condition or developmental history (i.e. concomitant illness, behavioral disorder, prematurity, uncontrolled seizure disorder) that in the opinion of the investigator, make it unsafe for the subject to participate or could impair study results

- 1. We will include individuals who are not yet adults (infants and children).

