# Data Management* and Confidentiality

- 1. Baseline and Final visit assessment scores will be compared. We will explore factors that may impact outcomes including reported frequency of use. Subjects may be stratified into groups based on such factors and sample group change averages will be compared.
  2. All source form data will be stored in locked cabinets in a locked office for the duration of the study. Electronic data entry will be stored on secured NCH research drive ([name]) and will be password protected.
  3. Data will be stored indefinitely
  4. Access to data: only investigators listed on IRB will be provided access to study materials.

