# Provisions to Protect the Privacy Interests of Subjects

- 1. Privacy: Subjects will be asked to complete NCH Neurology Media Consent form which allows them to determine how their image will be used or disseminated. Families may opt out of videotaped assessments through this form. Additionally, The study staff will be visiting the subjects’ homes, allowing them to receive highly personalized, innovative services in a completely private environment with no need to travel (travel is challenging for these families). Every effort will be made to protect the privacy of these subjects and their families.
  2. Making subject feel at ease: The families in this study are facing a very challenging diagnosis. By offering these patients a treatment that can strengthen their child and slow progress of the disease, this study will potentially be improving their lives. It is our experience that these families are very much at ease with the therapy teams that they work with.

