# Resources Available

- 1. We do not anticipate any difficulty reaching full enrollment. NCH SMA clinics occur twice monthly with roughly 8 patients per clinic (patients seen on a 6-month or 1-year basis).

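### The primary aim asks whether the harness system impacts motor performance, but a single-arm before-after comparison in children on disease-modifying drugs cannot attribute change to the device in either direction

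*Protocol*

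**What the plan says.** The Study Summary calls this a "Pilot interventional study". The Objectives section gives a two-part primary aim: "Our primary aim is to explore whether BWSS is a feasible modality for in-home use and whether it impacts motor performance". The secondary aim there asks whether frequency of use alters the treatment effect. Study Endpoints lists the gross motor scales as primary endpoints for utility, and Procedures Involved describes the study as looking at the effects of the home programme on motor performance.

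There is one group: "Subjects will be provided with one portable BWSS, manufactured by Enliten LLC, to be used in their home for a period of 6 months". Study Timelines sets motor assessments at baseline, a midpoint and month six. The comparison, given under Data Management and Confidentiality, is "Baseline and Final visit assessment scores will be compared". That section also says factors such as reported frequency of use will be explored and that children may be grouped by them.

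Eligibility requires "treatment with a disease modifying agent", with no minimum duration and no stable period. The Background says early gene-therapy results in type I disease "reported subject achievement of gross motor milestones beyond what would be expected for their diagnosis". The Confidential Health Information section recognises that time since treatment start may influence response and says this will be explored in the analysis.

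**The concern.** The verb *impacts* asks a causal question: what the device adds to what would have happened without it. The design observes only what happens with it. Other causes of change act over the same six months: the drug, growth and development, and the course of the disease. On the protocol's own account the drug can move the outcomes being measured, and a child may enrol soon after starting it.

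At stake is how the study will be read. A mean gain could be reported as a device benefit when the drug or age produced it. A flat result could be reported as no benefit when the device had offset decline. The secondary aim inherits the problem, because it presupposes a treatment effect that the design does not isolate.

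**Working it through.** **1. What the data identify.** Let δ be the device effect over six months and β the change that would have occurred without the device (drug, growth, disease course). With one group, the mean change estimates δ + β. This is one quantity with two unknowns. An observed mean gain of 0.3 SD fits each of these equally well:

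| δ (device) | β (background) | Sum |
|---|---|---|
| 0.3 | 0 | 0.3 |
| 0 | 0.3 | 0.3 |
| 0.6 | −0.3 | 0.3 |

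**2. Whether the planned explorations supply β.**
- *Time since drug start* (Confidential Health Information). This shows how change varies with drug timing among children who all have the device. It may explain part of the spread, but it gives no value for a child without the device.
- *Frequency of use* (Data Management and Confidentiality). Use is not randomised and in practice depends on the family and child, so it may follow the child's ability, health or progress. An association between use and change can arise with δ = 0.
- *The midpoint visit* (Study Timelines). This too is on-device time. No run-in or earlier assessment is planned.

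**3. Sign of β.** The Background describes SMA as progressive, and also describes stabilisation and improvement under newer drugs. It attributes natural skill gain to typically developing children and says weakness limits this in SMA. The documents therefore do not fix the sign of β.

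**4. Illustration of size.** The protocol gives no test, alpha, SD or expected change, so there is no figure to reproduce. *Assumptions:* δ = 0; β = d SDs of the change score; two-sided 5% paired t-test. *From the protocol:* n = 15 (Local Number of Subjects) and n = 50 (upper limit in the Study Summary).

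P(significant) = P(|T| > t₀.₉₇₅,ₙ₋₁), where T is noncentral t with n − 1 degrees of freedom and noncentrality d√n. Critical values are 2.145 (n = 15) and 2.010 (n = 50).

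| d assumed | d√15 | n = 15 | d√50 | n = 50 |
|---|---|---|---|---|
| 0 | 0 | 5% | 0 | 5% |
| 0.3 | 1.16 | 19% | 2.12 | 55% |
| 0.5 | 1.94 | 44% | 3.54 | 93% |

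A negative d of the same size gives the same percentages for a significant decline. Recruiting more children makes a wrong reading more frequent, so sample size is no cure.

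**5. Would a control arm be practical?** Assume 1:1 allocation, two-sided 5%, 80% power and the normal approximation. The detectable difference is (1.960 + 0.842)·√(2/n per arm) SD. With 25 per arm this is 2.802 × 0.283 = 0.79 SD. With 7.5 per arm it is 2.802 × 0.516 = 1.45 SD. A control would remove the bias, but at this size it would detect only large effects. A more modest aim is the proportionate remedy.

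**The case against.** The strongest reply is that this is a labelled pilot with an exploratory verb. It sets no hypothesis, significance level or success threshold, so no wrong answer is built in. That stands. A single arm suits the feasibility half of the aim, and the risk in the motor half is over-interpretation at reporting. It lowers the severity, but it does not make the causal wording answerable.

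A second reply is that drug timing and frequency of use are already to be explored, and that further covariate handling belongs in an analysis plan that is not to hand. The recognition is real. Neither exploration gives a no-device reference, however, and no analysis of these data alone can create one without outside assumptions.

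Two stronger readings are tempting.
- A reader might infer that a useless device would probably appear effective. The documents do not support this: the background gain is assumed, its sign is unsettled, and at 15 children the assumed range gives 19% to 44%, below one half.
- A reader might infer from the privacy section, which speaks of "a treatment that can strengthen their child and slow progress of the disease", that the protocol already asserts efficacy. That is reassurance text outside the objectives and analysis. The same sentence goes on to speak of potential improvement, and Potential Benefits to Subjects says only that benefit may occur. Softening it is an editorial matter.

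**Conclusion.** The concern holds as a mismatch between aim and design. As written, the motor half of the primary aim cannot be answered, because change in either direction cannot be attributed to the device. This conclusion rests only on the protocol's own text: one group, a baseline-to-final comparison, a mandatory drug without a stable period, and a stated link between drug treatment and motor gain. The percentages are illustrative and depend on the assumed test and background gain. The feasibility half is unaffected. The point should be fixed, but it does not invalidate the pilot.

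**What to change.** 1. **Reword the aims.** In the Study Summary, Objectives and Procedures Involved, change the motor part to: *describe change in motor performance during six months of in-home BWSS use*. State that change will not be attributed to the device. Reword the secondary aim as an association between use and change.
2. **Record drug history.** Collect the start date of the disease-modifying agent and any start, switch or addition. Show change with and without children who started or changed agent within six months before baseline or during the study. This extends the exploration of drug timing already planned.
3. **As support only, add earlier scores.** Where a clinic score on the same scale exists after drug start, show the pre-enrolment monthly rate beside the on-device rate. Resources Available describes "patients seen on a 6-month or 1-year basis", so some earlier visits should exist, but the protocol does not say which scales were recorded at them. Children recruited by flyer or word of mouth may have no chart at this clinic. Consent or authorisation must cover the chart data.

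Cost: protocol wording, a few data fields and some chart abstraction, with no added patients or study visits. The downside is a weaker claim, and many children may lack an earlier score.

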# Background

- 1. Spinal muscular atrophy (SMA) is an autosomal recessive disease involving the degeneration of lower motor neurons in the spinal cord that results in progressive muscle atrophy.1 SMA is characterized into four main phenotypes based on age of onset and highest motor milestone achieved: type I (unable to sit unassisted); type II (able to sit unassisted but unable to stand or walk independently); type III (walks independently); and type IV (adult-onset).2 Historically, a multidisciplinary treatment approach is aimed at limiting the trajectory of decline through proactive management of clinical manifestations.3,4 With newer technologies providing improved supportive care, it has been hypothesized that the expected phenotype for all types of SMA is evolving toward improved survival and optimized function.5 This maintenance approach to symptomatic management is also being driven to change as recent therapeutic advancements are making their way through the clinical trial pipeline. In December 2016, Spinraza® (nusinersin) became the first US FDA approved drug available for the treatment of SMA.6 This was quickly followed by the promising preliminary results for AVXS-101 gene replacement therapy in children with SMA type I, which reported subject achievement of gross motor milestones beyond what would be expected for their diagnosis.7 Both therapies target the preservation of existing motor neuron connections in the spinal cord and provide greater evidence for a changing phenotype of symptom stabilization and functional improvement that will require a new approach to clinical care.
  2. Physical therapists play a key role in the evaluation and management of musculoskeletal manifestations and functional impairments in children and adults with SMA. Recently published care guidelines stratify suggested categories of physical therapy assessment and interventions by functional ability (non-sitters, sitters, and ambulatory).3 These guidelines were created prior to this new treatment-era of SMA and are aimed at supporting the highest level of function, not towards facilitating development of strength, skill, and more advanced motor milestones. The reported success of SMA drug therapies suggest physical therapy interventions may now be aimed at motor milestone and gross motor development.
  3. Typically developing children naturally build strength and motor skills by exploring their environment through curiosity-driven mobility. Deficits in muscle strength limit independent and self-guided mobility in children with SMA due to the fact that their muscles are unable to support the whole weight of their own body. By unweighting a portion of their total body weight, children with SMA will be provided with an opportunity to begin activating the muscles in their legs and trunk, something they would otherwise be unable to do. Daily in-home use of a body weight support harness system may assist these children in building strength and developing new skills.

# Study Endpoints

- 1. Primary endpoints for feasibility include using a 5-question Likert-style scale survey of patient reported experience and documented frequency and duration of BWSS use. Primary endpoints for utility are assessments of gross motor function and include The World Health Organization’s gross motor developmental milestones, Bayley Scales of Infant Development v.3 Gross Motor subtests, Hammersmith Functional Motor Scale Expanded and/or Revised, and Neuromuscular Gross Motor Outcome.

# Study Intervention/Investigational Agent

- 1. Name of interventional agent: The Portable Mobility Aid for Children (PUMA); Body weight support harness system manufactured by Enliten, LLC
  2. The PUMA is a commercially available device that can safely be used to promote development in any child with a developmental delay. It provides mechanical support of a child’s body while allowing vertical and horizontal movement within the system’s frame. The BWSS was designed by an engineering company (Enliten, LLC). The BWSS is a metal structure that is connected to a harness worn by a child. The structure consists of four 7ft metal support beams (“legs”) that create a functional square footprint of 9ft by 9ft and adjustable heights up to 7ft 2in (Appendix D). The four legs are connected at the top by interconnected beams such that the system looks like a four legged square tent with flat top and no cover. A child wears a secure cloth harness that is connected to a moveable beam connected to the top of the metal structure. The connection between child/harness and metal structure is via springs, which provide body-weight support up to 50lbs. The moveable beam allows for movement throughout the square footprint. The secure cloth harness cradles the child’s entire torso for stability and comfort and will be adjusted according to each body type to provide safe movement.

Information regarding the concept, safety, and design of the BWSS as provided by Enliten LLC, can be found in Appendix E. Drug/Device Handling: If the research involves drugs or device, describe your plans to store, handle, and administer those drugs or devices so that they will be used only on subjects and be used only by authorized investigators.

# Procedures Involved*

- 1. This is a voluntary study investigating the feasibility and effects of a home-based functional exercise program using a body weight support harness system (BWSS) on motor performance in children treated for spinal muscular atrophy. Subjects will be provided with one portable BWSS, manufactured by Enliten LLC, to be used in their home for a period of 6 months. Subjects will engage in a BWSS use and document frequency / duration of use.
  2. **Screening/Baseline**: Subject demographic information and equipment safety check will be completed prior to the initial in-home visit. Baseline assessment of motor function may be completed at any time within a 3 week window prior to or during the initial in-home visit.

**Initial Visit (in-home):** A study team member will travel to the subject’s home to complete the BWSS set up. The BWSS Inspection Check List will be reviewed and signed by the responsible participating family member and the study team member. Pictures or video of the final set-up will be taken and stored in the subjects file. The participating family members will be trained on how to securely strap their child into the harness and on appropriate activities to engage in with their child while in the harness. They will be instructed on frequency and duration of treatment time and asked to document this information in the Daily Activity Log. They may be asked to attach an activity monitor to the harness.

Prior to completion of this visit, the following documentation will be completed: 1) Informed Consent; 2) BWSS Inspection Check List; 3) Pictures or video of BWSS set-up in home.

A study team member will contact the family between the baseline and midpoint assessment visit to ensure the family is comfortable with BWSS use. If the family has questions or concerns, they will be addressed by the study team member via Skype or video conference phone call. If determined necessary by the PI, a study team member will travel to the family’s home for an additional in-home visit.

**Midpoint Assessment Visit**: A study team member will complete functional outcome assessments and evaluate compliance with usage schedule. Daily Activity Log will be checked and completion will be documented.

Families will be given the option to complete the midpoint functional assessments during an in-home visit or during a regularly scheduled clinic or research appointment at NCH. Midpoint assessment visits may also occur remotely using approved video conferencing services. Photos and videos of the child performing motor skills will be accepted to incorporate into the midpoint assessment up to one week after the date of visit. Photo and video submissions will only be accepted for assessments performed remotely.

**Final Visit**: A study team member will complete final functional outcome assessments. Families will be given the option to complete the final functional assessments during the in-home visit or during a regularly scheduled clinic or research appointment at NCH. Final assessment visits may also occur remotely using approved video conferencing services. Photos and videos of the child performing motor skills will be accepted to incorporate into the final assessment up to one week after the date of visit. Photo and video submissions will only be accepted for assessments performed remotely.

Families will be provided with an opportunity to enter the Optional Enrollment Extension phase (see 6.2.1 point below).

If the family would like to continue enrollment but the BWSS is already assigned to another subject on the waitlist, the Final Visit will be completed as detailed in 9.2.1 and the family will be placed on the waitlist for re-enrollment.

6.2.1 **Final Visit - Optional Enrollment Extension:** Should the family choose to continue enrollment following the 6-month finial visit, the BWSS will remain in the family’s home until the family withdraws from the study or until BWSS equipment is needed for use with another subject.

Families will be asked to continue documenting BWSS use in Daily Activity Logs. Functional assessments may be performed, either in the home or during a regularly scheduled clinic or research appointment at every 6-9 months.

6.2.2 **Final Visit without Enrollment Extension:** A study team member will return to the family’s home to dismantle the BWSS unit. Prior to disassembly, a final equipment check using the BWSS safety Inspection Check List will be completed, reviewed, and signed by the study team member and responsible parent. Daily activity log will be checked and completion will be documented

- 1. All functional outcome assessments will be video recorded. Parents may also submit video evidence of motor skill attainment within 7 days of any remote study visit, should the child not perform on the date of the assessment due to child’s mood or behavior.
     - Parents will submit video evidence through secured email communication. Submitted videos will be stored on secured NCH research drive, alongside other assessment videos.
  2. FFamilies will be educated on appropriate activities to help engage with their child in the harness.

Each family will receive an Activity Ideas booklet to reference throughout the duration of the study (Appendix F).

- 1. Families will be asked to fill out the Daily Activity Log (Appendix G) each time the harness is used. The log will include information on the duration and frequency of BWSS use, activities completed with child while in BWSS, and any observed changes in child’s motor function
  2. Families may be asked to attach a motion sensor to the harness system.
  3. **Liability Waiver and Legal Agreement**: Families are to review and sign a liability waiver prior to in-home equipment set-up. This documentation to be created by Nationwide Children’s Hospital Corporate Legal Services department and addresses the expectations and responsibilities of the families to maintain the integrity of the BWSS for the duration of the study
  4. **Safety Considerations**
     - **Equipment Inspection**
       - Equipment will be required to pass study team member inspection using the BWSS Inspection Checklist provided by Enliten, LLC. (Appendix A)
       - Equipment safety checks will occur at screening (prior to in-home set up), baseline, and final visit. Photographs or video of in-home set up will be included in safety documentation.
       - It will be required that the BWSS Inspection Check List be completed by the study team member and reviewed and signed-off by the study team member and parent at baseline and final study visit.
     - **Adult Supervision**
       - Families are required to supervise their child while using the BWSS at all times.
     - **Family Training**
       - Families will be trained on use of the BWSS on their first home visit. Training will be conducted by an investigator on the study team and will involve: an overview of BWSS use; instructions on safely securing the child into the harness; application and technique for use of the bungee system; application and technique for use of counter-weight system; and adjusting the amount of body weight support.
       - Each family will receive an instruction manual detailing how to safely adjust the harness and amount of body weight support provided by the harness, to reference for the duration of the study (provided by Enliten, LLC; Appendix B and Appendix C).
       - Families will be instructed to leave the system as it was set-up in their home throughout the duration of the study. If the family needs to move or take down the BWSS, a safety check by a study team member will need to be completed prior to resuming use. This can be done as either an in-home visit or via a video conference call.
       - If needed, a member of the study team may call the subject’s parents to troubleshoot any technical difficulties that may arise. If the difficulties are not resolved over the phone, a member of the study team may schedule an in-home visit with the family. The family will be instructed not to use the system if they have any concerns about safety.

